Thus far, vitamin D and phosphate binding therapies have not yet been tested in a large randomized clinical trial powered to evaluate kidney disease outcomes. The Vitamin D/ Calcium Polyp Prevention Study is the ideal setting in which to test the effects of vitamin D and/or calcium on kidney function in a double blind, placebo controlled setting.

*10.6.2 Objectives*

The primary aim is to investigate the effect of calcium and/or vitamin D on the prevalence of microalbuminuria, a marker of kidney damage, at the end of 3 or 5 years of treatment with calcium and vitamin D, calcium alone or vitamin D alone versus placebo.

*Hypothesis: Vitamin D treatment will be associated with a lower prevalence of microalbuminuria.*

The secondary aims are as follows:

1. To evaluate the effects of calcium and/or vitamin D on blood pressure at the end of 3 or 5 years of treatment with calcium and vitamin D, calcium carbonate alone or vitamin D alone versus placebo.

*Hypothesis: Vitamin D therapy will be associated with significantly lower blood pressure.*

1. To evaluate the effects of calcium and/or vitamin D on kidney function as measured by serum creatinine measurements at baseline, year 1, year 3 and year 5 in all participants of the parent study with available creatinine measurements. Additional urine and serum markers of kidney function to be measured at the end of 3 to 5 years of treatment will include:
   1. Urine: markers of tubular damage including KIM-1 and NGAL
   2. Serum: creatinine (to be assayed at the lab used for baseline measurement),calcium and cystatin C, an additional marker of kidney function
   3. Serum: bone markers and other markers of kidney disease progression including serum phosphate, alkaline phosphatase, intact parathyroid hormone (PTH) and fibroblast growth factor-23 (FGF-23) levels.

*Hypothesis: Treatment with vitamin D and calcium will result in better kidney function compared to placebo*.

*10.6.3 Recruitment and Enrollment Procedures*

The parent study defines the pool of potential subjects and those subjects who are willing to participate will be consented at the in-person End-of-Treatment visit (which is part of the parent study procedures) prior to their 3-year or 5-year follow-up colonoscopy. Participants will be reimbursed $15 for their time and effort after completion of the specimen collection.

*10.6.4 Specimen/data Collection and Analysis*

10.6.4.a Urine collection

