**10.6.4.e Analyses**

*Measurement of Serum Creatinine, Calcium, Cystatin C, Phosphate. Alkaline phosphatase, FGF-23 and intact PTH*

At the Albert Einstein College of Medicine Institute for Clinical and Translational Research laboratory, specimens will be received and appropriately stored until analysis. Analyses will be batched and analyses will be performed once all of the specimens are received.

*Measurement of urinary albumin, creatinine, KIM-1 and NGAL*

Analyses will be batched and performed by the Albert Einstein College of Medicine Institute for Clinical and Translational Research laboratory using standard methods.

*10.6.5 Sample Size and Power*

Of the 2259 participants in the parent study, we plan to recruit approximately 900 into this sub-study. In the Framingham Offspring cohort with a mean age of 59 years, 12.2% had microalbuminuria, defined as at least 30 mg/g creatinine. [186](#_ENREF_186) In the NHANES III survey, which includes younger participants, 8.5% of participants had a urinary albumin:creatinine ratio greater than 30 mg/g.[187](#_ENREF_187) Assuming the background prevalence of microalbuminuria in the trial is 12% and an alpha of 0.05, we will have 80% power to detect a relative risk of 0.64 for microalbuminuria comparing the vitamin D groups to the placebo group with 900 participants. We will therefore aim to recruit 900 participants for the urinary albumin measurement. In the Framingham Offspring Study, the standard deviation for systolic blood pressure is approximately 20 mm Hg. [186](#_ENREF_186) Assuming an alpha of 0.05 and 900 participants, we will have greater than 85% power to detect a difference of 3 mm Hg between the vitamin D and placebo groups. For the repeated measures analysis for creatinine we will only use data from participants who have had all of their creatinines measured at the same laboratory (n≈1500). Having a sample size of 1500 for repeated measures analysis to evaluate changes in creatinine with an alpha of 0.05 gives us 90% power to detect a difference of 0.1 mg/dL in creatinine measurements. Evaluating changes in bone serum biomarkers, assuming an alpha of 0.05, we have >90% power to detect a difference of 1 standard deviation between the groups.

*10.6.6 Statistical Analyses*

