Specific Aim #1: All analyses will be performed and outliers will be verified by re-assay, if urine is available. Because this is a post-hoc analysis of a randomized clinical trial and data will not be available on the entire clinical trial population, we will create a table to evaluate whether baseline characteristics are equally distributed among the participants in the sub-study. The proportion of participants in each randomized group with microalbuminuria (defined as >30 mg/g creatinine) will be compared using a chi-square test. If there are imbalances in the baseline characteristics, we will perform a logistic regression with the outcome albuminuria adjusting for characteristics that were imbalanced at baseline. In addition, we will compare medication use at follow-up to evaluate whether there were imbalances in NSAID and ACE inhibitor and Angiotensin Receptor Blocker (ARBs) use between the randomized groups.

Specific aim #2: The mean blood pressure of the 3 measurements will be used for all analyses. Baseline characteristics of the randomized groups included in this sub-study will be compared. In addition, the use of anti-hypertensive medications at the time of the blood pressure measurement will be compared between the groups. We will first compare the systolic and diastolic blood pressures among the 4 randomized groups using ANOVA. We will also compare vitamin D to no vitamin D using Student’s t-test. If characteristics are not balanced between the groups, we will use multivariable adjusted linear regression to evaluate whether treatment had an effect on systolic and diastolic blood pressures separately.

Specific aim #3: All data will be checked for outliers and specimens will be re-assayed for extreme outliers. Creatinine measurements will be converted to estimated glomerular filtration rates using the CKD-Epi equation. [188](#_ENREF_188) We will compare the prevalence of CKD (defined as an estimated GFR <60 ml/min/1.73m2) between the 4 treatment arms using chi-square test. We will also used random effects models with repeated creatinine measures which can account for missing values to compare serial creatinines between the 4 treatment groups. To evaluate whether calcium and/or vitamin D supplementation over 5 years affected serum phosphate, alkaline phosphatase, intact PTH and FGF-23 levels, we will compare levels between the intervention groups and the placebo group using appropriate methods for skewed data.

*10.6.7 Human Subjects Research*

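### The kidney sub-study's stated 80% power for microalbuminuria is about 59% on its own inputs, and 10.6.6 plans no analysis of the albumin:creatinine ratio on its continuous scale

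*Protocol*

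**What the plan says.** Section 10.6.2 sets the aim: "The primary aim is to investigate the effect of calcium and/or vitamin D on the prevalence of microalbuminuria, a marker of kidney damage". Its hypothesis is "Vitamin D treatment will be associated with a lower prevalence of microalbuminuria".

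Section 10.6.5 gives the sample-size basis: "Assuming the background prevalence of microalbuminuria in the trial is 12% and an alpha of 0.05", then "we will have 80% power to detect a relative risk of 0.64 for microalbuminuria", the contrast being "comparing the vitamin D groups to the placebo group with 900 participants". The recruitment target of 900 is drawn from this statement. The same section also cites a survey prevalence of 8.5%.

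Section 10.6.6 gives the analysis: "The proportion of participants in each randomized group with microalbuminuria (defined as >30 mg/g creatinine) will be compared using a chi-square test". If baseline characteristics are imbalanced, a logistic regression on the same binary outcome follows. No analysis of the ratio itself is described, although 10.6.4.e has urinary albumin and creatinine measured in the laboratory. For serum phosphate, alkaline phosphatase, PTH and FGF-23, the same section says "we will compare levels between the intervention groups and the placebo group using appropriate methods for skewed data".

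**The concern.** The first problem is arithmetic. The power statement that justifies 900 participants does not follow from the prevalence, relative risk and sample size printed with it. If the true relative risk is 0.64, the planned test would miss it about four times in ten (41%), not one time in five. A null result would then be read against a sensitivity that the sub-study does not have.

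The second is a missed opportunity. Among the outcomes to which 10.6.6 assigns an analysis, albuminuria is the only one with nothing planned on its continuous scale. Blood pressure is compared by means, creatinine by random-effects models as well as by a threshold, and the bone and mineral markers as levels. A binary outcome with about 12% of people above the cut uses little of what the assay provides. If a continuous analysis is added only after a null chi-square result, it will carry little weight.

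**Working it through.** **Inputs.** Background prevalence 12%, relative risk 0.64, 900 participants, alpha 0.05 (all 10.6.5). Prevalence under vitamin D: 0.12 × 0.64 = 0.0768. Assumed: a two-sided test (10.6.5 does not say) and 450 v 450, because vitamin D is allocated equally in both the full-factorial and the two-arm component.

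**The plan's figure, 80%, does not reproduce.** Power = Φ[(p₁ − p₂ − 1.96·SE₀)/SE₁].
- Mean prevalence = (0.12 + 0.0768)/2 = 0.0984.
- SE₀ = √(2 × 0.0984 × 0.9016/450) = 0.01986.
- SE₁ = √[(0.12 × 0.88 + 0.0768 × 0.9232)/450] = 0.01981.
- Power = Φ[(0.0432 − 0.0389)/0.0198] = Φ(0.216) = **58.6%**.

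**Other readings of the same text.**

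| Reading | Power |
|---|---|
| Unpooled variance / arcsine / log relative risk | 58.8% / 59.0% / 57.6% |
| One-sided 0.05 | 70.3% |
| 0.64 taken as an odds ratio | 51.0% |
| Placebo-only 225 v all others 675 | 50.9% |
| Placebo-only 225 v both vitamin D arms 450 | about 45% |
| Four groups, 3 degrees of freedom | 41.9% |
| 8.5% prevalence, 450 v 450 | 43.7% |

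Two readings do give 80.3%, but neither matches the text: 12% placed in the vitamin D group (controls 0.12/0.64 = 18.75%), and 1,500 participants in total.

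**What 80% would need.**
- Sample size per group = [1.96·√(2 × 0.0984 × 0.9016) + 0.8416·√(0.1056 + 0.0709)]²/0.0432² = (0.8256 + 0.3536)²/0.001866, which gives 746, or about 1,490 in total. That is about 66% of the 2,259 parent-study participants named in 10.6.5; 900 is about 40%.
- Holding 450 v 450, the detectable relative risk is 0.548 (12% v 6.6%), or about 0.55.

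**The continuous scale.** The protocol gives no mean, SD or distribution for the ratio, so the following is conditional. Suppose the log ratio is normal with equal SDs and vitamin D lowers it by the same amount in everyone.
- Shift implied by 12% v 7.68%: Φ⁻¹(0.9232) − Φ⁻¹(0.88) = 1.427 − 1.175 = 0.252 SD.
- Power = Φ(0.252 × √225 − 1.96) = Φ(1.82) = 96.6%. A rank test gives about 96% by simulation.
- At 8.5% prevalence the shift is 0.231 SD and power 93.5%.
- If 30% or 50% of values lie at an assay floor, power is about 93% or 89%.

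If the same 0.252 SD shift acts only on the upper part of the distribution (simulated, 450 v 450):

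| Effect confined to | t-test on log ratio | Chi-square on prevalence |
|---|---|---|
| Upper 75% | 84% | 60% |
| Upper 50% | 51% | 59% |
| Upper 30% | 22% | 59% |
| Upper 20% | 12% | 58% |

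The two tests break even when the effect reaches about the upper 55% (about 60% each).

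**The case against.** The strongest defence is that prevalence is the question asked. Section 10.6.2 names it in the aim and the hypothesis, and the chi-square test matches. Section 10.6.1 gives a clinical reason: the presence of microalbuminuria is one of its two criteria for chronic kidney disease, which it links to cardiovascular events, mortality and end-stage disease. Participants are described in 4.1 as healthy, and severe kidney disease is excluded in 4.8. Nothing in the protocol shows that vitamin D lowers albumin within the normal range. All of this stands, and it is why prevalence should remain primary.

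A reader might infer that the 30 mg/g cut throws away some 37 points of power, 59% against 96%, and that the log ratio should replace the primary aim. The documents do not support that. The 96% needs a distribution and a uniform effect that the protocol nowhere supplies, and under an effect confined to raised values the ranking reverses. Nor is albuminuria the only marker cut at a threshold: 10.6.6 also compares the proportion with estimated GFR below 60. The difference is that creatinine is analysed serially as well.

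It may also be said that 450 v 450 is an assumption, since 10.6.5 speaks of the placebo group and 10.6.6 of each randomised group. That is so, but the other readings tried give lower power, so it does not rescue the 80%. Finally, this is an ancillary study that describes itself as post hoc. That limits the consequence but does not make the power figure right.

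**Conclusion.** The 80% in 10.6.5 is wrong as written. For a relative risk of 0.64 from 12% with 900 participants, power is about 59%, assuming 450 v 450 and a two-sided test, and no reading tried that fits the text reaches 80%. That the background rate was placed in the wrong group, or that a total of 1,500 was used, would explain the figure, but either is only an inference.

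The absence of any continuous analysis of the ratio is a gap worth closing, not an error in the choice of primary endpoint. How much a log-ratio analysis would gain cannot be settled from the documents: it could be large under a uniform shift and negative under an effect confined to raised values. The point concerns the sub-study's primary aim only.

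**What to change.** 1. In 10.6.5, restate the power as about 59% for a relative risk of 0.64, or give the detectable relative risk as about 0.55 at 80% power. Name the contrast as vitamin D v no vitamin D, and use the same contrast in 10.6.6.
2. In 10.6.6, keep the prevalence above 30 mg/g as the primary aim. Add a pre-specified one-degree-of-freedom comparison of log albumin:creatinine ratio, vitamin D v no vitamin D, stratified by full-factorial or two-arm component. Report it as a ratio of geometric means, with a rank test as check.
3. State beside it that about 96% power applies only under a uniform shift in a normal log ratio, and that the analysis is less powerful than prevalence if the effect is confined to roughly the upper half of the distribution or less.

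The cost is wording and one more analysis to report and interpret alongside prevalence, with the possibility that the two disagree. No extra samples, visits or assays are needed. The addition should be fixed before treatment comparisons of the urine results are seen.

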All potentially eligible individuals identified by a review of colonoscopy and pathology records will be assigned a study identification number prior to initial patient contact. The ID number will be in the form SC - RS - ##### . The “SC” is a number ranging from 01-99 and identifies the Study Center from which the subject was recruited. The “RS” is a number ranging from 01- 99 and corresponds to the specific recruitment site. The “#####” ranges from 00001-99999 and identifies the individual subject. This number is generated using a modulo 11 method that prevents the occurrence of sequential numbers in order to reduce errors from typing mistakes. If an individual is subsequently enrolled in the study then this same ID number will be used throughout the study. In addition, upon enrollment the subject will also be assigned a two letter study identification code consisting of the first initial of the subject’s first name followed by the last letter of the subject’s last name. This code will be used along with the subject’s study ID number in communications between the Dartmouth Project Coordination Center and the Study Center coordinators.

*4.7 Inclusion criteria*

1. One or more histologically verified neoplastic polyp (adenoma) that is at least 2 mm in size removed from the large bowel with the entire large bowel examined by colonoscopy and documented to be free of further polyps or areas suspicious for neoplasia within 120 days of study entry
2. Anticipated colonoscopic follow-up three years or five years after the qualifying colonoscopy
3. Age between 45 and 75 years at enrollment
4. (Women)Agreement to avoid pregnancy (i.e. use of standard contraception)
5. Willingness to forego calcium supplementation (including multivitamins containing calcium) or, for women only, option of taking calcium supplementation of 1200 mg/daily (contained in the study pills)
6. Willingness to forego vitamin D supplementation (including multivitamins containing vitamin D)
7. Agreement to daily dietary intake of the equivalent of not more than 1200 mg calcium
8. Agreement to daily dietary intake of the equivalent of not more than 400 IU vitamin D
9. Blood calcium level within normal range
10. Blood creatinine level not to exceed 20% above upper limit of normal
11. Serum 25-(OH)-vitamin D within lower limit of 12 ng/ml to upper limit of 90 ng/ml

12) Ability and willingness to follow the study protocol, as indicated by provision of informed consent to participate

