13) Good general health, with no severely debilitating diseases or active malignancy that might compromise the patient's ability to complete the study

*4.8 Exclusion criteria*

(General exclusionary criteria:)

1. Participation in another colorectal (bowel) study (intervention study) in the past 5 years
2. Current participation in any other clinical trial (intervention study)
3. Pregnancy or lactation
4. A diagnosis of narcotic or alcohol dependence in the past 5 years
5. A diagnosis of dementia (e.g. Alzheimers) in the past 5 years
6. A diagnosis of a significant psychiatric disability (e.g. Schizophrenia, refractory bipolar disorder, current severe depression) in the past 5 years

(Exclusions due to derangement of calcium metabolism or indications/contraindications to study agents)

1. Any diagnosis of kidney stones
2. A diagnosis of granulomatous diseases, e.g. sarcoidosis, active chronic fungal or mycobacterial infections (tuberculosis, histoplasmosis, coccidioidomycosis, blastomycosis), Berylliosis, Wegener’s granulomatosis in the past 5 years
3. A diagnosis of hyperparathyroidism or other serious disturbance of calcium metabolism in the past 5 years
4. A diagnosis of severe kidney disease, e.g. chronic renal failure in the past 5 years
5. A diagnosis of unexplained hypercalcemia in the past 5 years
6. Any diagnosis of osteoporosis with physician recommendation for treatment of low bone mass
7. A diagnosis of two or more low trauma fractures in the past 5 years
8. A diagnosis of a medical condition requiring treatment with vitamin D (e.g. osteomalacia) in the past 5 years

(Exclusions due to intestinal or bowel problems:)

1. Any diagnosis of invasive carcinoma of the large bowel (even if confined to a polyp)
2. Any diagnosis of familial colorectal cancer syndromes, e.g. Familial Adenomatous Polyposis (FAP) (including Gardner syndrome, Turcot’s syndrome), Hereditary Nonpolyposis Colorectal Cancer (HNPCC), Hamartomatous Polyposis syndromes (including Peutz-Jeghers or Familial Juvenile Polyposis)
3. Any diagnosis of inflammatory bowel disease, e.g. Crohn’s Disease, Ulcerative Colitis
4. A diagnosis of chronic intestinal malabsorption syndromes, e.g. celiac sprue, bacterial overgrowth, chronic pancreatitis, pancreatic insufficiency in the past 5 years
5. Any large bowel resection

(Exclusions due to poor health:)

1. A diagnosis of malignancy, other than non-melanoma skin cancer in the past 5 years

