4. Subjects will be sent materials describing this new development. All subjects who were randomized into the study will be sent these materials with the sole exception of deceased subjects. The materials include:

a. Letter to Subject with Normal Creatinine Result

b. Letter to Subject with Above Normal Creatinine Result

c. Above normal creatinine result with specific result and lab range

d. Significant New Information/Findings sheet for Pre-EOT subjects

e. Significant New Information/Findings sheet for Post-EOT subjects

f. Post-EOT Additional Study Visit Consent

1. Subjects who choose to discontinue study calcium treatment will be urged to continue study vitamin D treatment.

6.3.2 April 11, 2012 modification to the creatinine criteria and procedures to be used due to the Unanticipated Problem

1. Because many of the local laboratories used for creatinine measurements in the study do not take sex, age or race into account, the creatinine reference ranges provided by those laboratories may not be appropriate for the individual subject. Therefore, the criteria for stopping study calcium treatment (randomized or two-arm) has been changed to an increase of 0.3 mg/dL or more from baseline (update to #1 in section 6.3.1 above, originally implemented in October 2011).
2. Similarly, subjects who complete or who already have completed the treatment phase of the study and whose last creatinine level in the study was increased by 0.3 mg/dL or more from baseline will be invited to return for a blood draw to re-measure the levels (update to #3 in section 6.3.1 above, originally implemented in October 2011).
3. In place of annual study blood draws during the treatment phase or a study visit after completion of the treatment phase, creatinine (and calcium) levels may be documented from medical records.

*6.4 Colonoscopy*

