Whenever possible, subjects should be fasting prior to all study blood draws (e.g. no food or beverage intake other than water for 8 hours prior to the blood draw). Regardless, the time of last food or beverage consumption will be collected. Customized prepackaged bar-coded kits will be provided containing materials for collecting, processing, and aliquoting the blood samples. Blood samples will be collected according to standard operating procedures at each Study Center and sent to local labs for analysis or promptly frozen at -20C or below pending transfer to a -70C freezer for storage until shipment to the UCLA Nutrition Research Center Laboratory or the NCCC Clinical & Molecular Pharmacology Shared Resource Laboratory. Each individual blood specimen will be bar-coded and tracked electronically from the time of collection at the Study Center. Biospecimen transport will adhere to stringent shipping standards. The Study Centers, study laboratories (at UCLA and USC), and the biospecimen storage facility at the NCCC will be equipped with at least one bar code reader for logging and tracking specimens.

As necessary for all study blood draws, a re-draw may be required to collect blood if the original specimen is lost, destroyed, damaged, or if a re-analyses is required (e.g., albumin measurement to estimate ionized calcium at Year 1 or Year 3 safety assessment).

*9.3 Methods for Laboratory Procedures*

*Measurement of Calcium and Creatinine*

Blood levels of creatinine, total calcium, and albumin will be measured according to standard procedures at the local clinical laboratories. The normal reference ranges of the local laboratories will be used for eligibility assessment at enrollment and safety assessment at year 1 and, where applicable, year 3 (for those with a 5 year follow-up colonoscopy interval).

*Measurement of Vitamin D*

25-Hydroxy-Vitamin D Determination:

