In addition, creatinine and calcium measurements previously performed on all randomized subjects in the parent study at baseline, year 1, and year 3 (for subjects with a 5 year follow-up colonoscopy) will be used in these analyses. Creatinine and calcium measurements will also be performed on blood samples collected on all randomized subjects in the parent study at the Year 3 and Year 5 End-of-Treatment visits and used in these analyses.

*10.6.1 Background*

Chronic kidney disease (CKD), assessed by either the presence of microalbuminuria or decreased kidney function, affects over 23 million people in the United States and is associated with a high risk of hypertension, cardiovascular events, mortality and progression to end-stage renal disease. Known risk factors for kidney disease include the presence of high blood pressure, diabetes mellitus, dyslipidemia, non-white race and older age. Novel risk factors for kidney disease progression are continuously being identified, including low 25-hydroxyvitamin D (25(OH)D) levels and elevated serum phosphate and FGF-23 levels.[175-177](#_ENREF_175)

Animal studies suggest plausible mechanisms whereby low 25(OH)D levels and high phosphate levels may be harmful. Activated vitamin D, 1,25-dihydroxyvitamin D (1,25(OH)2D), suppresses renin biosynthesis in mice and vitamin D deficiency stimulates renin production.[178](#_ENREF_178) In different animal models, 1,25(OH)2D or its analogs reduced proteinuria levels, preserved glomerular podocyte structure, [179](#_ENREF_179) decreased levels of transforming growth factor β1, an inducer of renal fibrosis, and inhibited mesangial cell proliferation, a marker of renal injury. [180](#_ENREF_180) High phosphate levels in rats lead to worse kidney function.[181](#_ENREF_181) In the setting of kidney disease, vitamin D supplementation may lead to higher phosphate levels through increased gut absorption but calcium therapy can act as a phosphate binder in the gut and may prevent a rise in phosphate levels in those treated with vitamin D.

High blood pressure can be both a consequence of kidney disease and can independently cause kidney disease. Low vitamin D levels have been associated with the development of incident high blood pressure. [182](#_ENREF_182) Some trials of vitamin D therapy have noted lower blood pressures in the vitamin D treated group. [183-185](#_ENREF_183) However, these trials had small sample sizes and were not powered to evaluate changes in blood pressure.

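### The kidney sub-study compares crude prevalence of eGFR below 60 across four arms, though that level is admissible at entry, baseline creatinine is available, and the arms differ by design in their share of women

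*Protocol*

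**What the plan says.** Section 10.6.6, third aim, first turns creatinine into eGFR: "Creatinine measurements will be converted to estimated glomerular filtration rates using the CKD-Epi equation". It then fixes the categorical outcome and its test: "We will compare the prevalence of CKD (defined as an estimated GFR <60 ml/min/1.73m2) between the 4 treatment arms using chi-square test". No one is excluded for being below 60 at entry, no baseline term enters, and no visit or repeat value is named. The first two aims in that section provide for adjusted regression if baseline characteristics are imbalanced; the CKD comparison has no such provision. A separate analysis covers the continuous measure: "We will also used random effects models with repeated creatinine measures which can account for missing values to compare serial creatinines".

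The entry criterion in section 4.7 is: "Blood creatinine level not to exceed 20% above upper limit of normal". Section 9.3 says whose limit applies: "The normal reference ranges of the local laboratories will be used for eligibility assessment at enrollment". Section 6.3.2 says of those ranges that "many of the local laboratories used for creatinine measurements in the study do not take sex, age or race into account". The kidney exclusion in section 4.8 is "A diagnosis of severe kidney disease, e.g. chronic renal failure in the past 5 years"; no eGFR threshold appears. Section 10.6 says the sub-study will use "creatinine and calcium measurements previously performed on all randomized subjects in the parent study at baseline, year 1, and year 3". Section 10.6.5 limits the repeated-creatinine analysis to participants whose values all come from one laboratory, about 1500 people.

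**The concern.** A prevalence outcome at follow-up mixes disease present before treatment with disease arising on treatment. If the threshold lies inside the range admitted at entry, some participants count as cases whatever their allocation did, and the contrast shrinks towards zero. Adjusting for a baseline value already held removes much of this at almost no cost.

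The second problem is the phrase about four treatment arms. Women who chose the two-arm component all receive calcium (section 5.2). Pooled by treatment received, the calcium arms contain a non-randomized extra group of women. A crude calcium versus no-calcium difference then reflects sex and component as well as treatment. For the main endpoint, section 13.5 avoids this by leaving those women out of the calcium comparison. Section 10.6.6 does not repeat that safeguard.

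At stake is the reading of a kidney-function result on calcium: a null finding could be dilution, and a difference could be sex mix.

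**Working it through.** **Stated figure.** No rate, power or sample size is given for the CKD comparison. The nearest figure is 90% power for 0.1 mg/dL creatinine with about 1500 participants (section 10.6.5). It cannot be reproduced because no SD is given. Solved backwards for 750 v 750, SD = 0.1 × √(750/2) / (1.96 + 1.28) = 0.60 mg/dL. This does not bear on the CKD test.

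**1. Is eGFR below 60 admissible at entry?**
The protocol names the equation without coefficients. I assume the 2009 creatinine form, non-black, which above the sex-specific constant k is

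eGFR = 141 × (creatinine/k)^-1.209 × 0.993^age (× 1.018 for women), with k = 0.9 for men and 0.7 for women.

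Mean age is 58.1 (section 10.6.7.a), and 0.993^58.1 = 0.665. The local upper limits are not given and are assumed.
- Men, limit 1.3: cap 1.2 × 1.3 = 1.56; 141 × (1.56/0.9)^-1.209 × 0.665 = 141 × 0.514 × 0.665 = 48.
- Women, limit 1.1: cap 1.32; 141 × (1.32/0.7)^-1.209 × 0.665 × 1.018 = 141 × 0.464 × 0.665 × 1.018 = 44.

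| Assumed upper limit (mg/dL) | eGFR at the cap, age 58.1 |
|---|---|
| Men 1.1 / 1.3 / 1.5 | 59 / 48 / 41 |
| Women 0.9 / 1.1 / 1.3 / 1.5 | 56 / 44 / 36 / 30 |

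Below 60 is admissible at mean age for every limit in the table. At age 45 the lowest limits (men 1.1, women 0.9) just exclude it, at 65 and 62. A woman of mean age at 1.1 mg/dL, without the 20% allowance, is at 55.

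**2. What share of end-of-treatment cases was below 60 at entry?**
The documents give no creatinine or eGFR distribution, assay error or rate of decline, so this is simulation under assumptions, with no treatment effect.
- Mean creatinine 1.00-1.10 (men) and 0.80-0.90 (women), between-person SD 0.13-0.15, within-person SD 0.05-0.10 mg/dL, four years of ageing, upper limits 1.3 and 1.1: end-of-treatment prevalence 5-20%, of which 33-65% were below 60 at entry.
- Mean eGFR 80-90, SD 12-16, error 3-8%, decline 0.8-2.0 per year, various upper limits: the share below 60 at entry falls to about 10% or less with fast decline or low limits, and reaches 48%. Counting also those truly at or above 60 at the end but measured below, the range is 14-72%.

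**3. Sex mix of the four arms.**
From the schema in section 3.2:
- Placebo, and vitamin D alone: 84/(360 + 84) = 84/444 = 18.9% women.
- Calcium, and calcium plus vitamin D: (84 + 312)/(360 + 84 + 312) = 396/756 = 52.4% women.

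Shift in crude prevalence with no treatment effect = (0.524 − 0.189) × (prevalence in women − prevalence in men). In the first set of simulations above, the low end is 7.3% v 3.0%, giving 0.335 × 4.3 = 1.4 points. The high end is 21.9% v 11.3%, giving 0.335 × 10.6 = 3.5 points. The size and direction depend on the assumed sex difference; the imbalance of women does not.

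**4. What would a baseline-aware outcome gain?**
Assumptions: mean eGFR 85, SD 14, error 6%, decline 0.8 per year, upper limits 1.3 and 1.1, 750 v 750, and a 0.05 mg/dL shift in everyone.
- Prevalence 7.5% v 11.4%: SE = √(2 × 0.0945 × 0.9055/750) = 0.0151; z = 0.039/0.0151 = 2.58; power about 0.74 (unrounded inputs).
- New cases among those at or above 60 at entry (about 718 per group), 4.6% v 8.2%: SE = √(2 × 0.064 × 0.936/718) = 0.0129; z = 0.036/0.0129 = 2.79; power about 0.80.
- With a 0.03 mg/dL shift the two powers are 0.33 and 0.38.
- Baseline-adjusted continuous creatinine exceeds 0.99 in both cases.

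**The case against.** The strongest reply is that the aim does not rest on this test. The random-effects model of serial creatinine uses baseline, is the only creatinine analysis given a power statement, and in the illustration is far more powerful. That stands. It limits the importance of the point, but it does not repair the CKD comparison, which is a different outcome.

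It is also right that disease at entry is balanced in expectation within each randomized component, so type I error there is preserved. A reader might infer that pre-existing cases bias the result; within a component they only dilute it. The bias argument applies only to the pooled calcium comparison. Nor are participants below 60 at entry wholly uninformative: some may rise above 60, which matters for a hypothesis of better kidney function.

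A reader might also infer that most recorded cases would be pre-existing or noise. The documents supply none of the inputs needed for that. Likewise, reading the outcome as resting on a single value is an inference: no repeat is required, but none is ruled out.

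Finally, this is not the trial's safety instrument. After the Unanticipated Problem, section 6.3.2 adopted a rise of 0.3 mg/dL from baseline, so a baseline-referenced categorical measure already exists. The choice of outcome and test might be called detail for an analysis plan, but section 10.6.6 states both explicitly.

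**Conclusion.** The point holds as a structural weakness of one secondary analysis in an ancillary study; the main trial is unaffected. Two things follow from the protocol with few assumptions. First, eGFR below 60 lies inside the entry range for any plausible upper limit at the mean age, and the planned test ignores a baseline value that is held. Second, the pooled arms differ by design in women, 52% against 19%. Section 10.6.7.a reports 37% women rather than the planned 40%, so the realized split may be somewhat narrower.

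The sizes are conditional. The share of cases already below 60 at entry runs from well under half to about two thirds. The null shift from sex mix is about 1.4-3.5 points under the creatinine assumptions shown. The power gain from a baseline-aware outcome is modest: 0.74 to 0.80, or 0.33 to 0.38. A much larger gain, from about 0.52 to 0.75, can be produced by placing a 3-point effect entirely in new cases (13.4% v 16.4% with 1130 per group, against 5.5% v 8.5% with 1015). That is a constructed case and should not be expected.

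**What to change.** In section 10.6.6, third aim, make the main CKD comparison a logistic regression of end-of-treatment eGFR below 60 on treatment, with baseline eGFR as covariate, stratified by randomization component (full factorial or two-arm, as randomized). Draw calcium contrasts from full-factorial subjects only, in line with section 13.5; vitamin D contrasts can use both components. Name the visit that supplies the outcome value.

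Use baseline and follow-up creatinine from the same laboratory, as section 10.6.5 already requires for the repeated-measures analysis, or present that restriction as a sensitivity analysis. This matters because section 9.1 places creatinine in local laboratories while section 10.6.4.e also lists it for central batch assay.

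Report new eGFR below 60 among those at or above 60 at entry as a supporting analysis, and keep crude prevalence as description.

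The cost is analysis wording; no new measurements are needed. The same-laboratory restriction reduces the sample to about 1500, calcium contrasts lose the two-arm women, and the supporting analysis drops those below 60 at entry and still includes chance crossings by people just above it.
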